#### 2.4.3. Sample size

A total of 342 patients with non-metastatic BC are required, based on the following assumptions: an estimated compliance rate of 59% [5] in patients with non-metastatic BC one year after the first prescription of ET, a bilateral alpha of 5%, and statistical power of 80%; to show a 15% difference in compliance between patients in the intervention arm and those in the control arm 1 year after the first prescription, it is necessary to include 155 patients per arm (bilateral chi-squared test). Taking into account a loss to follow-up rate of 10%, a total of 171 patients will be included in each arm (nQuery Advisor V7).

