**Methods:**

In this study, we will include 342 women with non-metastatic hormone receptor–positive BC with an indication for treatment with ET. Patients will be randomly assigned 1:1 by minimization and stratified by age, stage, type of ET prescribed, and presence of comorbidities (or not) in two arms. The intervention will consist of numerical HRQoL assessment using the CHES (Computer-based Health Evaluation System) software before each consultation (with delivery of scores to clinicians) coupled with therapeutic information. Therapeutic information will consist of three workshops related to understanding the prescription, nutrition, and fatigue. A reminder letter will be sent to patients every month. Patients in the control group will follow standard care. HRQoL will be assessed using a classic “paper-pencil” collection at baseline in both arms to ensure comparability between arms and at 12 months. The primary endpoint is 12-month compliance with ET. Patient satisfaction with care and the clinicians’ perception of the usefulness of routine HRQoL assessment will also be assessed.

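### At the stated 10% loss, 171 patients per arm leave about 154, not the 155 that the plan calls necessary; the effect on power is very small and a restatement is enough.

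*Protocol article*

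**What the plan says.** The sample size section (2.4.3) of the protocol article assumes "an estimated compliance rate of 59% [5] in patients with non-metastatic BC one year after the first prescription of ET" and aims "to show a 15% difference in compliance between patients in the intervention arm and those in the control arm". The test is two-sided at 5%, with 80% power. On these terms "it is necessary to include 155 patients per arm (bilateral chi-squared test").

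The section then adds the allowance for attrition: "Taking into account a loss to follow-up rate of 10%, a total of 171 patients will be included in each arm". It opens with the resulting total: "A total of 342 patients with non-metastatic BC are required". The Methods paragraph of the Abstract repeats this total: "we will include 342 women with non-metastatic hormone receptor–positive BC".

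The section names the software, nQuery Advisor, but gives no formula for turning 155 into 171.

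**The concern.** An allowance for loss is meant to ensure that, if the assumed fraction drops out, the required number of evaluable patients remains. Here the three printed figures (155 required, 10% lost, 171 enrolled) fail that check: taking 10% from 171 leaves fewer than 155.

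What is at stake is the consistency of the trial's headline sample size. The figure appears in the Abstract and in section 2.4.3, it is likely to be carried into the results report, and any reader can find the mismatch with one multiplication. If the gap were large, the stated power would be wrong as well, so its size has to be worked out.

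**Working it through.** **Inputs** (section 2.4.3; the 1:1 ratio is from section 2.2)

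- Control compliance at 12 months: p1 = 0.59
- Intervention compliance: p2 = 0.59 + 0.15 = 0.74, reading the 15% as an absolute gain
- Two-sided alpha 0.05, so z = 1.96; power 0.80, so z = 0.8416
- Allocation 1:1, chi-squared test
- Loss 10%; enrolled 171 per arm, 342 in total

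**Step 1. Reproduce 155.** With pooled variance, no continuity correction and mean rate (0.59 + 0.74)/2 = 0.665:

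n = [1.96 × √(2 × 0.665 × 0.335) + 0.8416 × √(0.59 × 0.41 + 0.74 × 0.26)]² / 0.15² = 154.24, rounded up to 155.

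This matches the plan exactly. It also supports the reading of the inputs: a continuity correction would give 168, and a 15-point fall instead of a rise would give 174. Any discrepancy therefore lies in the allowance for loss, not in the base size.

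**Step 2. Apply the stated loss to the stated enrolment.**

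- Per arm: 171 × 0.90 = 153.9
- In total: 342 × 0.90 = 307.8, against 2 × 155 = 310
- In whole patients: 171 − 17 = 154 (loss 17/171 = 9.9%) and 171 − 18 = 153 (loss 18/171 = 10.5%), so one to two below 155 per arm

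**Step 3. Find the loss that 171 can absorb.** 1 − 155/171 = 16/171 = 9.4%.

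**Step 4. Find the enrolment that 10% loss requires.** 155 / 0.90 = 172.2, rounded up to 173 per arm and 346 in total. This is 2 more per arm and 4 more overall than stated.

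**Step 5. See how 171 could have arisen.**

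| Route | Result | Rounding needed to reach 171 |
|---|---|---|
| 155 × 1.10 | 170.5 | up |
| 154.24 / 0.90 | 171.4 | down |

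Both give 171, and the article does not say which was used.

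**Step 6. Power at the numbers left.** With n evaluable per arm,

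power = Φ{[0.15 × √n − 1.96 × √(2 × 0.665 × 0.335)] / √(0.59 × 0.41 + 0.74 × 0.26)}

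| Evaluable per arm | Power |
|---|---|
| 153 | 79.7% |
| 154 | 79.9% |
| 155 | 80.2% |

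Against 155, the loss of power is 0.3 points at 154 and 0.5 points at 153.

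**The case against.** The strongest reply is that this is rounding. The true requirement is 154.24, and 155 already gives slightly more than 80% power. Measured against 154.24, the 153.9 patients left fall short by 154.24 − 153.9 = 0.34 of a patient per arm. At the whole-percent precision that the plan uses, 79.7% and 79.9% are both 80%. The 10% loss and the 59% compliance rate are planning estimates, far less certain than the difference between 9.4% and 10%. All of this stands, and it limits the point to a correction of wording. It does not make the printed figures agree: the section itself calls 155 necessary, and 171 with 10% lost does not deliver 155, nor quite the unrounded 154.24.

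Two stronger readings are tempting, and the document supports neither.

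- A reader might infer that the authors multiplied by 1.10 where they should have divided by 0.90. The match with 170.5 rounded up is exact, but no formula is given, and a correct division of 154.24 by 0.90 followed by rounding down gives the same 171. The mechanism is a possibility, not a finding.
- A reader might infer that the trial is underpowered and must recruit more. A change of 0.3 to 0.5 points, to a value that still rounds to 80%, does not support that.

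**Conclusion.** The point holds as a minor figure that is wrong as written. The stated enrolment, loss rate and required number do not agree, and nothing elsewhere in the article corrects this. The shortfall is one to two evaluable patients per arm at 10% loss, with power of 79.7% to 79.9% against the stated 80%. By either route to 171, the conclusion is the same.

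It rests on three assumptions: the 15% is an absolute difference, and the test is an uncorrected chi-squared (both supported by the exact match at 155); and a patient lost to follow-up contributes no 12-month compliance result, which is the ordinary meaning of such an allowance. No design decision or trial conclusion depends on the discrepancy.

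**What to change.** Keep 342 and restate what it provides. In section 2.4.3, replace the sentence on loss with one saying that 171 patients per arm retain the required 155 if no more than 16 of 171 (9.4%) are lost, and that at 10% loss about 154 per arm remain, with about 79.9% power. It would also help to state how 171 was calculated.

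The cost is one sentence: no extra patients, and no change to design, recruitment or the total in the Abstract. The alternative of 173 per arm (346 in total) would make the 10% allowance literally correct, but four more patients for about 0.3 points of power are not needed.

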#### 2.4.4. Data collected

Sociodemographic characteristics (age, sex, level of education, family situation, socio-professional category, and work time), medical and surgical history, date of tumor diagnosis, tumor characteristics, previous treatments, patient clinical characteristics at inclusion and at each follow-up visit (weight, height, and overall patient condition), concomitant treatment, type of ET received, HRQoL data (FACT-G), anxiety and depression (HADS), social support (SSQ6), treatment modification (change in the type of ET), treatment-related toxicities, and their grade will be collected. Patient satisfaction with provided care will be measured using the EORTC-SAT-C33 and the EORTC-OUT-PATSAT-7. Clinician perceptions of systematic HRQoL assessment (utility and perceived satisfaction, reasons for use or non-use, and the intention to adopt it in practice) will be collected via an ad-hoc questionnaire. Sociodemographic data and reasons for refusing to participate will be documented for patients who refuse to participate. Data on patient withdrawal or death will be documented in the case report form. Reasons for study withdrawal should also be documented. All data from this study will be transcribed in an electronic case report form (Clinsight).

### 2.5. Questionnaires and tools

#### 2.5.1. EORTC-QLQ-C30 and EORTC-QLQ-BR23 questionnaires

The cancer-specific EORTC-QLQ-C30 questionnaire and its BC-specific QLQ-BR 23 module are available in French and are validated tools to assess HRQoL in cancer and more specifically in BC [29]. The EORTC-QLQ-C30 questionnaire makes it possible to assess one dimension of HRQoL/overall health, five functional dimensions (physical, current activities, cognitive, emotional, and social), eight dimensions of symptoms (fatigue, nausea and vomiting, pain, dyspnea, insomnia, loss of appetite, constipation, and diarrhea), and a scale of financial difficulties. The EORTC-QLQ-BR23 consists of 23 questions which assess four functional dimensions (body image, sexual activity, sexual pleasure, and future perspectives) and four dimensions of symptoms (side effects of systemic therapy, breast symptoms, symptoms at the arm, and upset by hair loss). Scores are generated per dimension in accordance with the EORTC [30] scoring rules. These scores vary from 0 (worst) to 100 (best) for the functional and global health parameters and from 0 (best) to 100 (worst) for symptom parameters.

#### 2.5.2. MGL questionnaire

The four-item MGL Medication Adherence Scale was developed by Morisky et al. [31] to measure adherence to treatment. It has a range of 0 to 4, where 0 is very low and 4 is highest. Patients are categorized according to three levels of adherence: high (score equal to 4), moderate (score equal to 2 or 3), and low (score equal to 0 or 1).

#### 2.5.3. HADS questionnaire

The HADS is an instrument for detecting anxiety and depressive disorders. It was validated and adapted in French by Lepine et al. [32] in 1989. This scale has 14 items rated from 0 to 3 and covers two dimensions. Seven questions are related to the anxiety dimension and seven are related to the depressive dimension, yielding two scores: A (anxiety) and D (depression). The maximum score for each dimension is 21. A score of 11 or higher indicates the probable presence of the disorder.

#### 2.5.4. FACT-G questionnaire

The FACT-G is a 27-question tool validated in patients with cancer and has four subscales to assess well-being. The FACT-G instrument assesses four HRQoL domains: physical well-being (seven items), social or family well-being or both (seven items), emotional well-being (six items), and functional well-being (seven items). Respondents use a 5-point Likert-type scale which rates the relevant domain from 0 (not at all) to 4 (very much). From these subscales, a global score is obtained [33, 34]. The FACT-G total score varies from 0 to 108. The higher the score, the better the HRQoL.

#### 2.5.5. EORTC PATSAT-C33 and EORTC-OUT-PATSAT-7 questionnaires

The EORTC-PATSAT-C33 questionnaire and its EORTC-OUT-PATSAT7 ambulatory context-specific supplementary module were developed to assess perceptions of patients with cancer regarding the quality of care received [35]. They consist of 33 and 7 items, respectively. The EORTC-PATSAT-C33 questionnaire includes three sections on the perceived quality of care provided by physicians, radiotherapy nurses/technicians, and services/care organization. The clinician section includes three dimensions that address technical skills (three items), quality and quantity of information exchanged (three items), and behavior (four items). The radiotherapy nurses/technicians section has two dimensions: information provision and reactivity (three items) and affective behavior (four items). The service and organization of care section has three dimensions: coordination (four items), interaction with the health-care team (seven items), and five single items.

The complementary EORTC-OUT-PATSAT7 includes two dimensions dealing with convenience of care (three items) and transition (three items) and a single item on continuity of care. The instructions invite patients to evaluate the most recent care experience and to specify the cancer care setting. The score varies from 0 to 100. A higher score indicates higher level of satisfaction.

#### 2.5.6. SSQ6 questionnaire

Social support will be evaluated by the SSQ6 questionnaire, validated and adapted in French by Rascle et al. in 2005 [36]. This questionnaire reflects the support available in patients’ environment. Social support is measured across two dimensions: support availability, through the number of contacts that the patient can count on (0 to 9 people), and quality of support, through patient satisfaction with support received.

Each item represents a situation in which the patient may need support. The patient is asked to cite the number of people that she could count on in that particular situation. Concerning the second item, the patient is asked to assess satisfaction with the support provided. The scores are generated in accordance with Sarason’s recommendations. A score is calculated for each dimension. The support availability score is calculated as the sum of the number of people available for the six items; this score ranges from 0 to 54, with 54 representing the highest availability. The social support satisfaction score is calculated by the sum of the satisfaction of the six items; this score ranges from 6 to 36, with 36 representing the highest level of satisfaction [37].

#### 2.5.7. Ad-hoc questionnaire

This ad-hoc questionnaire, derived from the work of Velikova and colleagues [19, 28], will assess the perception of doctors concerning the interest of systematic HRQoL evaluation. It evaluates the following criteria: usefulness of the systematic evaluation of HRQoL, perceived satisfaction with systematic evaluation of HRQoL, reasons to use it (or not) in current clinical practice, and whether to adopt it routinely.

#### 2.5.8. CHES

For this study, a French version of the CHES web-based solution will be available. Each patient will be represented by an identifier to guarantee data confidentiality and anonymous exploitation of the database for statistical purposes. CHES offers a cross-sectional presentation (presentation of scores for each dimension) and a presentation of the longitudinal course of HRQoL for each dimension of the questionnaires. CHES also minimizes input errors, reduces the number of missing data related to data collection, and avoids ambiguities in the responses. This software also allows remote access via a platform that will let patients (outside the consultations) give an input on their HRQoL in the event of a deterioration or improvement perceived at the clinical level.

#### 2.5.9. Follow-up

Patients who receive adjuvant ET will attend a consultation every 6 months, and HRQoL assessment will be performed at each visit. As the aim of this project is to integrate this intervention in daily clinical practice, it will be performed in agreement with patients’ routine follow-up. Patients will complete the questionnaires prior to each consultation, either at home via access to the web portal within 24 h before consultation or at the time of consultation. During consultation, the physician will have access to the results immediately, via the secure web portal, and will be able to discuss them with the patient.

### 2.6. Statistical analyses

#### 2.6.1. Descriptive analysis

A descriptive analysis of patients’ clinical and sociodemographic characteristics at inclusion will be performed for each arm. Data will be expressed as number and percentage for categorical variables and as mean ± standard deviation or as median and interquartile range for continuous variables, as appropriate. The number of missing data will be specified. The number of patients with available data will also be specified for quantitative variables. Normality will be tested by using the Shapiro–Wilk test. According to data distribution, independent Student *t* tests or non-parametric Mann–Whitney tests will be used to compare results between groups. The basic categorical characteristics will be compared using tests of chi-squared or Freeman Halton according to the number of the variable categories. Continuous variables can be transformed into categorical variables according to thresholds defined by the literature.

#### 2.6.2. HRQoL analysis

All HRQoL scores will be calculated according to FACT-G guidelines and described according to the arm (interventional arm or control arm). A logistic regression model will be used to assess the capacity of HRQoL to predict 12-month compliance with ET. The modulatory potential of social support on compliance will be assessed using an interaction term between the availability/satisfaction of social support that patients receive and HRQoL in a logistic regression model. The modulatory potential of psychological distress on compliance will be assessed using an interaction term between patient anxiety/depression and HRQoL in a logistic regression model.

An analysis of missing HRQoL data profiles will also be performed. If a missing not at random (MNAR) profile is demonstrated/suspected, multiple imputation of missing data can be performed in sensitivity analysis, taking into account the variables associated with the occurrence of missing data.

The significance level for the statistical analyses is fixed at a *P* value of less than 0.05, and all tests will be bilateral. The data analysis will be performed by using Statistical Analysis System (SAS) version 9.4 (SAS Institute Inc., Cary, NC, USA).

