### 2.1. Inclusion procedure

The study will be proposed to eligible patients by their doctors (oncologists, surgeons, and radiation oncologists). Patients will be included at the time of the first prescription of ET (at the end of the treatments by surgery with or without chemotherapy with or without radiotherapy). Once included, patients will be randomly assigned to one of the two study arms (interventional arm or control arm). Patients then will be referred to the clinical research associates, whose role will be to collect patient data (clinical and sociodemographic) in both study arms and to instruct patients in the interventional arm on how to use the CHES (Computer-based Health Evaluation System) software [26]. For patients who wish to access the platform from home, a username and password will be provided. If needed, clinical research associates will assist patients to complete HRQoL questionnaires. This information will be collected in the case report form to take into account social desirability bias.

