#### 2.4.2. Secondary endpoints

The secondary endpoints will be anxiety and depression assessed by the Hospital Anxiety and Depression Scale (HADS) questionnaire, social support assessed by Sarason’s Social Support Questionnaire (SSQ6) questionnaire, and HRQoL assessed by the FACT-G questionnaire. HRQoL data using the FACT-G questionnaire will be assessed at inclusion in both arms to ensure comparability between groups and at 12 months to assess the predictive value of HRQoL on compliance with ET. Patient satisfaction with care will be assessed by the EORTC-SAT-C33 and EORTC-OUT-PATSAT-7 questionnaires. Physician perception regarding the utility of systematic HRQoL evaluation will be assessed using an ad-hoc questionnaire derived from the work of Velikova [19, 28], including the perceived utility and satisfaction of routine assessment HRQoL, reasons for use/non-use, and the intention to adopt this assessment in routine care.

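### The HRQoL prediction model rests on FACT-G, with the month-12 value assigned to prediction; the only HRQoL measured on ET before the outcome has no planned analysis here

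*Protocol article*

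**What the plan says.** The Background sets, as a later step, the aim of assessing whether HRQoL can predict compliance with ET. For the model, section 2.6.2 says: "A logistic regression model will be used to assess the capacity of HRQoL to predict 12-month compliance with ET". That sentence names neither instrument nor time point, but the one before it does name the instrument: "All HRQoL scores will be calculated according to FACT-G guidelines and described according to the arm".

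Section 2.4.2 supplies the timing. For inclusion: "HRQoL data using the FACT-G questionnaire will be assessed at inclusion in both arms to ensure comparability between groups". For the second measurement: "at 12 months to assess the predictive value of HRQoL on compliance with ET". Inclusion itself is fixed in section 2.1: "Patients will be included at the time of the first prescription of ET". The primary endpoint in 2.4.1 is compliance at 12 months.

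A second set of HRQoL scores exists. Women in the intervention arm complete the QLQ-C30 and BR23 before each consultation (2.3.1). Section 2.5.9 gives the rhythm: "Patients who receive adjuvant ET will attend a consultation every 6 months, and HRQoL assessment will be performed at each visit". The Discussion counts three assessments over the study. The BR23 has "four dimensions of symptoms (side effects of systemic therapy, breast symptoms, symptoms at the arm, and upset by hair loss"), and section 2.5.1 scores both instruments by EORTC rules. The data list in 2.4.4 names one HRQoL instrument only: "type of ET received, HRQoL data (FACT-G), anxiety and depression (HADS"). QLQ-C30 and BR23 are absent from the secondary endpoints (2.4.2), the data list (2.4.4) and the analyses (2.6.1 to 2.6.3).

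**The concern.** A predictor should be measured before what it predicts. Section 2.4.2 uses the month-12 FACT-G for a month-12 outcome, so any association could run in either direction: poor HRQoL may lead a woman to skip tablets, or skipping tablets may change how she feels. If the social-support and distress interaction models in 2.6.2 take the same HRQoL value, they inherit the problem.

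The inclusion FACT-G avoids this but describes women at the end of primary treatment, before ET can have affected them. The trial's rationale is that HRQoL seen during ET can be acted on, and the Background names side effects as one source of poor compliance. The mid-study QLQ-C30/BR23 bears directly on that, is already collected, and appears in no planned analysis. A null FACT-G result could then be reported as HRQoL not predicting compliance, although HRQoL on ET before the outcome was never examined.

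**Working it through.** **Timing of each HRQoL measure**

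| Measure | Arms | On ET? | Before the outcome? | Planned use in the article |
|---|---|---|---|---|
| FACT-G at inclusion (2.1, 2.4.2) | both | no | yes | comparability of arms |
| FACT-G at month 12 (2.4.2) | both | yes | no, concurrent | prediction of compliance |
| QLQ-C30/BR23 between inclusion and month 12 (2.3.1, 2.5.9) | intervention | yes | yes | feedback and alerts; no analysis |

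Only the third row meets both conditions.

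**The plan's own figure (2.4.3).** Compliance 59% against 74%, two-sided 5%, power 80%, chi-squared test with pooled variance, mean rate 0.665:

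n = [1.960 × √(2 × 0.665 × 0.335) + 0.842 × √(0.59 × 0.41 + 0.74 × 0.26)]² / 0.15² = (1.308 + 0.555)² / 0.0225 ≈ 154.2, rounded up to 155 per arm.

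This matches the stated 155. The enrolled 171 is 155 × 1.10 = 170.5, rounded up. The point here disputes neither figure.

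**What a one-arm model could detect.** For one normally distributed score in a logistic model, the smallest detectable log odds ratio per SD is (1.960 + 0.842) / √(n p (1 − p)).

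- Intervention arm, n = 155, p = 0.74: √29.82 = 5.461; 2.802 / 5.461 = 0.513; odds ratio 1.67 (or 0.60 for a score where higher is worse). Non-compliers: 155 × 0.26 = 40.3.
- Intervention arm if compliance were only 59%: √37.49 = 6.123; 2.802 / 6.123 = 0.458; odds ratio 1.58. Non-compliers: 155 × 0.41 = 63.6.
- FACT-G in both arms, n = 310, p = 0.665: √69.06 = 8.310; 2.802 / 8.310 = 0.337; odds ratio 1.40.

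**Effect of adjustment.** Adjusting for a covariate correlated r with the score divides the detectable log odds ratio by √(1 − r²). The documents give no r. Taking 0.5 to 0.7 as an assumption:

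- r = 0.5: 0.513 / 0.866 = 0.592; odds ratio 1.81.
- r = 0.7: 0.513 / 0.714 = 0.718; odds ratio 2.05.

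With about 40 non-compliers there is room for one score and one adjustment term, not for several scores each with its own baseline.

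**The case against.** The separation of instruments looks deliberate. QLQ-C30/BR23 is the intervention tool; FACT-G is the study measure, on paper, in both arms and withheld from clinicians (2.3.3). Describing scores by arm is possible only for FACT-G. This stands, and it is why FACT-G should remain the main model.

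A reader might infer that the prediction objective cannot be met as planned. The documents do not support that: the objective does not specify HRQoL measured on ET, and the inclusion FACT-G precedes the outcome in both arms. A reader might also infer that the CHES scores go wholly unused, or that side effects of ET are otherwise unrecorded. Neither follows. The scores drive feedback and alerts, section 2.5.8 leaves statistical use of the database open, and 2.4.4 lists treatment toxicities with their grade, though these are not an HRQoL measure.

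An exploratory one-arm model might also sit in the full protocol or analysis plan, so its absence from a condensed article would not by itself be a finding. What remains is what the article does state: a concurrent measure assigned to prediction, and a scoring sentence covering all HRQoL scores that does not fit the EORTC scoring in 2.5.1.

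The exact visit is also not fixed. Section 2.5.9 says every six months, the Discussion says two or three consultations a year, and the text does not say whether a CHES score is taken at inclusion. Women are randomised and only then taught the software (2.1). Fig. 1 may settle this; it was not available for this check.

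Finally, clinicians see the scores, and falls in score trigger self-help tools or alerts (2.3.1). A poor score may prompt help that restores compliance and so weakens the association. This limits what the added model can show.

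**Conclusion.** The point holds in a limited form. As written, the article assigns prediction to a FACT-G value concurrent with the outcome, and no planned analysis uses HRQoL that is both on ET and before the outcome. The mid-study QLQ-C30/BR23 in the intervention arm would fill that gap, with modest precision: a detectable odds ratio of about 1.67 per SD unadjusted, and about 1.8 to 2.05 after adjustment under the assumed correlations, against about 1.40 for FACT-G in both arms. These figures assume 155 evaluable women per arm, compliance at the design rates, complete scores and a normally distributed predictor. The issue concerns a secondary objective.

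**What to change.** 1. In 2.4.2 and 2.6.2, name the inclusion FACT-G as the predictor in the main prediction model, in both arms, and call the relation between month-12 FACT-G and compliance a concurrent association.
2. Add one supportive, exploratory model in the intervention arm: 12-month compliance on a single pre-chosen QLQ-C30/BR23 score from the consultation between inclusion and month 12 (about month 6), for example BR23 systemic-therapy side effects. Score it by EORTC rules and adjust for inclusion FACT-G, or for the first CHES score if one is taken at inclusion.
3. Restrict the scoring sentence in 2.6.2 to FACT-G, and list the CHES scores in 2.4.4.
4. State the limits with the result: one arm, about 155 women and about 40 non-compliers, the detectable odds ratio, and scores that clinicians and alerts act on. A null result therefore does not show that HRQoL fails to predict compliance.

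The cost is a data export, one more model and a few changed sentences. No new data are collected.

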#### 2.6.3. Sensitivity analysis

Contamination-based intent-to-treat analysis will be conducted to account for potential cross-contamination between the arms.

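### Section 2.6.2 answers suspected MNAR in the HRQoL scores with an imputation that, as described, assumes MAR, and sets a trigger that observed data cannot establish

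*Protocol article*

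**What the plan says.** Section 2.6.2 of the protocol article (HRQoL analysis) has FACT-G scores calculated and described by arm. For inference it states: "A logistic regression model will be used to assess the capacity of HRQoL to predict 12-month compliance with ET". Two further logistic models add interactions of HRQoL with social support and with anxiety or depression.

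On missing data the same section says: "An analysis of missing HRQoL data profiles will also be performed". It continues: "If a missing not at random (MNAR) profile is demonstrated/suspected, multiple imputation of missing data can be performed in sensitivity analysis", and this is to be done "taking into account the variables associated with the occurrence of missing data".

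The only other sensitivity analysis is in section 2.6.3: "Contamination-based intent-to-treat analysis will be conducted to account for potential cross-contamination between the arms". It does not concern missing data.

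**The concern.** The text fixes a trigger (MNAR), a remedy (multiple imputation) and one ingredient of the imputation model (predictors of missingness). The remedy does not fit the trigger. MNAR means that missingness still depends on the unseen score after everything observed has been taken into account. An imputation built on observed predictors assumes that no such dependence remains.

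The setting makes this relevant. FACT-G at 12 months is collected on paper (section 2.3.3), and the Background cites a study linking poorer HRQoL to non-adherence. Women who feel worse may well be less likely to return the form. If the complete-case and imputed results agreed, the trial report could present that as robustness to MNAR when no departure from MAR had been examined.

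**Working it through.** **1. Trigger against remedy.** Let Y be the 12-month score, X the observed variables and R = 1 if Y is observed.

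- MAR: P(R = 1 | Y, X) = P(R = 1 | X).
- MNAR: P(R = 1 | Y, X) still depends on Y.
- Imputation from X draws missing scores from f(Y | X, R = 1). That equals f(Y | X, R = 0) under MAR and in general does not under MNAR.
- A profile of missing data can show that R depends on X. That is evidence against missing completely at random. It cannot separate MAR from MNAR, because Y is unseen wherever R = 0. MNAR can be suspected on clinical grounds but not demonstrated from the data.

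**2. Size for a mean score (illustration).** The article gives no FACT-G SD, baseline-to-12-month correlation or missingness rate, so every input here is an assumption and results are in SD units.

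Setting A: 15% missing; odds of missing multiplied by 2 or 3 per SD lower 12-month score; correlation with baseline 0.5 to 0.7.

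- Complete-case bias: 0.096 to 0.143 SD.
- Bias after imputation on baseline: 0.052 to 0.108 SD, so 23% to 47% is removed.

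Setting B: 20% missing; log-odds of missing 0.5 or 1.0 per SD.

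| Correlation | Log-odds per SD | Complete-case bias | Bias after imputation | Removed | Shift still needed in imputed values |
|---|---|---|---|---|---|
| 0.3 | 0.5 | 0.095 | 0.089 | 6% | -0.444 |
| 0.3 | 1.0 | 0.173 | 0.159 | 8% | -0.793 |
| 0.6 | 0.5 | 0.095 | 0.062 | 35% | -0.308 |
| 0.6 | 1.0 | 0.172 | 0.114 | 34% | -0.571 |

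Removed = 1 - (bias after imputation / complete-case bias); first row, 1 - 0.089/0.095 = 6%. Remaining bias = fraction missing × size of the shift; first row, 0.20 × 0.444 = 0.089. The observed data cannot supply that shift. When the same simulation made missingness depend on baseline instead (MAR), imputation left a bias of at most 0.004 SD.

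**3. Size for the planned regression.** Here HRQoL is the predictor x and compliance C the outcome. Among complete cases:

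odds(C = 1 | x, R = 1) = odds(C = 1 | x) × P(R = 1 | x, C = 1) / P(R = 1 | x, C = 0).

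- If missingness depends on the score alone, the last ratio is 1 and the slope is unbiased.
- If it depends on compliance alone, the ratio is constant and only the intercept moves.
- The slope is distorted when the ratio changes with x, which needs missingness to depend jointly on HRQoL and compliance.

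A simulation of Setting A agrees (assumed true log-odds ratio 0.4 per SD, compliance observed, correlation 0.5 or 0.7). Slopes were 0.402 to 0.404 with full data, 0.400 to 0.405 in complete cases and 0.408 to 0.414 after imputation. Joint dependence was not simulated, so no size is given for it.

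**4. The plan's own figures.** None bears on this point. The sample size in section 2.4.3 concerns the primary endpoint and does not change.

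**The case against.** The best defence is that the sentence is condensed. Multiple imputation can be run under MNAR with delta-adjusted or pattern-mixture models, SAS 9.4 supports this, and a full protocol or SAP may specify it. That is true of the method in general. But the sentence names no shift, pattern or selection term, and the one ingredient it does name is the MAR one. A plan that followed it literally would run a MAR analysis in response to suspected MNAR. Good auxiliary variables would reduce the bias without removing it.

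Other parts of the defence stand, and they limit the point. A reader might infer four stronger things that the article does not support:

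- **That the primary endpoint is affected**, since section 2.4.3 allows for 10% loss to follow-up. The quoted rule covers HRQoL data only. The article does not describe how missing compliance data will be handled, and an article may leave that to the full protocol or SAP.
- **That imputation is withheld when data look MAR.** The text is silent on that case and prohibits nothing.
- **That the plan claims to test MNAR.** It does not say so, and the analysis is worded as optional. The misleading step would come in interpretation.
- **That 0.05 to 0.11 SD is the harm to the planned inference.** It is bias in a mean score. Under the same assumptions the regression slope is essentially unharmed.

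**Conclusion.** The rule is wrong as written. It pairs an MNAR trigger, part of which can never be met from the data, with an imputation that as described is valid under MAR. Section 2.6.3 does not repair this. Agreement between complete-case and imputed results would not be evidence of robustness to MNAR.

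The reach is the secondary HRQoL analyses: scores described by arm, and the logistic models of 12-month compliance on HRQoL with their interactions. For mean scores, residual bias is 0.05 to 0.11 SD in Setting A and 0.06 to 0.16 SD in Setting B. Both ranges rest wholly on assumed inputs; the direction follows from the definitions. For the logistic slope, bias would arise mainly if missingness depends jointly on HRQoL and compliance, and its size is unknown. The primary compliance comparison and the sample size are untouched. Severity: moderate.

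**What to change.** Reword the missing-data paragraph of section 2.6.2 in three steps.

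1. Name multiple imputation as the MAR analysis. Include arm, baseline score, the minimisation factors, 12-month compliance and the predictors of missingness. Compliance must be in the model because it is the outcome of the logistic regressions; leaving it out would pull the slope towards zero.
2. Pre-specify a delta-adjusted (pattern-mixture) imputation with a tipping point as the MNAR sensitivity analysis. Let the shift differ by arm and by compliance status. The second matters because joint dependence on HRQoL and compliance is what would distort the slope.
3. Delete the condition that MNAR be demonstrated or suspected, so that both analyses are run in any case.

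The cost is protocol and SAP wording plus a little extra programming in the software already named (SAS 9.4). No new data are needed.
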